| Statistical Analysis  | Categorical data will be summarized by frequencies and percentages, and continuous variables by means and standard deviations (or medians and interquartile ranges for non-linear data). For the primary analysis, we will perform linear regression, adjusted for sex and intraoperative opioid MME to assess the comparison between trial groups. A modified intention-to-treat analysis will be employed, including only patients who received the block, and excluding patients with prolonged intubation. Sensitivity analyses using complete intention-to-treat and per protocol populations will also be conducted.                                                                                                                                                                                                                                                                                                                                                                                                                                                                                                                                                                                                                                                                                                                                                                                                                                                                                                                                                                                                                                                                                                                                                                                                                                          |

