One of the major limitations of nerve blocks administered via single doses of local anesthetic is their limited duration of action. For example, one prospective study of 113 participants undergoing cardiac surgery receiving ultrasound-guided deep PIP blocks with 40 mL 0.33% ropivacaine demonstrated a mean effective duration of a mere 17 hours [35]. One previous randomized study of 116 patients has investigated the role of continuous superficial PIP blocks in cardiac surgical patients, finding a significant reduction in time to extubation, time to mobilization, length of ICU stay, length of hospitalization, nausea/vomiting, pain scores at rest and with movement, and sufentanil/flurbiprofen consumption [36]. One other study investigated the potential for re-dosing of the superficial PIP block, randomizing 80 patients to ultrasound-guided superficial PIP block versus placebo on postoperative days 0 and 1. The authors demonstrated a reduction in pain scores, but were unable to show a significant reduction in opioid requirements over 48 hours nor incidence of delirium [29].

As such, there is still equipoise on the role of intermittent superficial PIP blocks in the multimodal approach to analgesia following cardiac surgery, and consequently guidelines are limited in the recommendations that can be provided on the use of such interventions [37]. The purpose of the present randomized trial is to definitively establish the clinical efficacy of

intermittent superficial PIP blocks with ropivacaine in optimizing postoperative pain control amongst a large population of patients undergoing cardiac surgery via median sternotomy.

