### 3.4 Tertiary (exploratory) Endpoints

- Time from catheter insertion to extubation
- Time from catheter insertion to first opioid analgesic provision following extubation
- Time from catheter insertion to mobilization
- ICU and hospital LOS
- Postoperative nausea and vomiting, measured via a 10-point visual analogue scale BID and antiemetic medication requirements up to 72 hours following catheter insertion
- Opioid requirements post-discharge as assessed by prescriptions provided at time of discharge and during post-discharge follow-up visit using both patient health record and direct patient recounting
- Chronic post sternotomy pain/disability and patient reported outcomes assessed at 3 months  $\pm$  4 weeks from surgery with McGill Pain Questionnaire as well as at 6 weeks  $\pm$  2 weeks and 3 months  $\pm$  4 weeks with the change in PROMIS 29 score (Attempts to obtain the 3-month data can continue for up to 6 months post-surgery before it will be considered a protocol deviation or the participant deemed lost-to-follow-up)

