## **7. Statistical Analysis and Sample Size Calculation**

For the primary analysis, we will perform linear regression, adjusted for sex (clinical stratification factor) and intraoperative opioid MME to assess the comparison between trial groups, with a P-value threshold of 0.05 being considered significant. If residuals indicate substantial violations of the linear regression assumptions, alternate methods will be attempted, such as analyzing log-transformed data, using bootstrap hypothesis testing or two-sample t-tests without equal variance. A modified intention-to-treat analysis will be employed, including only patients in whom a block catheter was placed, and a dose of study drug was administered. The time-to-event outcomes will be modelled simultaneously using a multistate framework. This approach will handle competing risks, such as death, and treat other non-fatal events, that could be related to each other, as intercurrent events. Sensitivity analyses using complete intention-to-treat and per protocol populations will also be conducted. Categorical data will be summarized by frequencies and percentages, and continuous variables by means and standard deviations (plus medians and interquartile ranges for non-symmetric data).

In order to detect a mean difference of 10 MMEs, assuming a standard deviation of 25 and an alpha value of 0.05, a sample size of 133 participants per group would be required to provide a power of 90%. Assuming an attrition rate of 25%, approximately 340 patients will need to be randomized for the primary modified intention-to-treat analysis.

Pre-specified subgroup analyses of the primary outcome include:

- Age
- Race/Ethnicity
- Sex/Gender
- Diabetes status
- BMI
- Type of operation
- Site

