## 3.2 Analysis Populations

### 3.2.1 Modified Intent-to-Treat (mITT) Population

The mITT Population will include all randomized participants in whom a block catheter was placed, and a dose of study treatment was administered. Treatment classification will be based on the randomized treatment assignment. The mITT Population will be the primary population used for the efficacy analyses.

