### 3.4.1 *Primary Efficacy Endpoints*

#### Primary Analysis

The primary efficacy endpoint is the cumulative postoperative opioid use measured as MMEs during the 72 hours following catheter insertion. The conversion of different opioids into MMEs will utilize the table provided in the study protocol.

Administered opioids are documented in the CRF on a daily basis; i.e., the date and time of each administered drug is not recorded. In contrast, the date and time of catheter insertion is recorded in the CRF. Consequently, opioid use for each participant will include those that were administered:

- The day of catheter administration
- The two days following the day of catheter administration
- A fraction of the third day following the day of catheter administration. The fraction will depend on the time of day that the catheter was inserted at the beginning of the 72 hour time interval. For example, if 40 MMEs were administered on the 3rd day and the catheter was inserted at 9:00 AM on day 0, the MMEs on the third day that will be included in the primary efficacy analysis would be  $(9/24) \times 40 = 15$  MMEs.

To assess the primary efficacy endpoint, the primary estimand is defined by the following key attributes:

- **Treatment:** 0.2% ropivacaine versus placebo
- **Target Population:** participants who are randomized into the study and received any amount of study treatment
- **Analysis Population:** The mITT Population
- **Intercurrent events:** premature treatment discontinuation, rescue nerve block, death
- **Analysis set and handling of intercurrent events:** Treatment policy strategy will be used. All available MME values during the 72 hours following catheter insertion will be used in the calculation of cumulative postoperative opioid use
- **Population level summary:** The difference in LS mean cumulative postoperative opioid use during the 72 hours following catheter insertion between treatment groups

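### The protocol synopsis excludes patients with prolonged intubation from the primary population, whereas protocol Section 7 and the SAP keep them

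*Combined protocol and SAP*

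**What the plan says.** The current protocol defines the primary population twice. In the Statistical Analysis row of the synopsis, the modified intention-to-treat (mITT) analysis is "including only patients who received the block, and excluding patients with prolonged intubation". In Section 7 it is "including only patients in whom a block catheter was placed, and a dose of study drug was administered", with no intubation criterion.

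The SAP (version 1.0, 06FEB2026, later than the protocol of 30 OCT 2025) agrees with Section 7. Its Section 3.2.1 reads: "The mITT Population will include all randomized participants in whom a block catheter was placed, and a dose of study treatment was administered". The primary estimand in SAP 3.4.1 targets "participants who are randomized into the study and received any amount of study treatment", and on intercurrent events it says: "Treatment policy strategy will be used". SAP 3.1.6 and the sensitivity analysis in 3.4.1 treat delayed extubation as an event to be modelled jointly with opioid use, not as a reason to remove anyone.

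The first exploratory endpoint in protocol Section 3.4 is "Time from catheter insertion to extubation". In Section 2, the protocol describes a 116-patient randomised study of continuous superficial blocks as "finding a significant reduction in time to extubation", among other benefits.

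**The concern.** A dosed patient with a long intubation is in the primary analysis under Section 7 and the SAP, and out of it under the synopsis. All three cannot be followed, and no clause says which prevails.

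The synopsis rule is also the weaker one statistically. It selects patients on something observed after randomisation and after the first bolus, which the protocol's own rationale says the block might change. If the block speeds extubation, the rule removes more saline than ropivacaine patients. If those removed also have unusual opioid use, the retained arms are no longer comparable as randomised. The rule has no time limit either, so who would be removed is not fixed in advance.

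**Working it through.** **1. The definitions side by side**

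| Place | Catheter and dose required | Prolonged or delayed extubation |
|---|---|---|
| Protocol synopsis | Block received | Excluded; no cut-off |
| Protocol Section 7 | Yes | Not mentioned; kept |
| SAP 3.2.1 | Yes | Not mentioned; kept |
| SAP 3.4.1 estimand | Any amount of study treatment | Not on the list of intercurrent events; kept |
| SAP 3.1.6 and 3.4.1 sensitivity analysis | As mITT | Kept and modelled jointly; no cut-off |

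The synopsis stands alone. Neither prolonged intubation nor delayed extubation is defined anywhere.

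**2. Timing.** Randomisation is preoperative (protocol 5.2, Visit R). Catheters go in after skin closure, and the first bolus is given at that time (synopsis, Study Intervention). Length of intubation is known only afterwards, so it is a post-treatment variable.

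**3. Could treatment affect it?** Time to extubation is an endpoint, the cited continuous-block trial reported a reduction, and Section 2 lists prolonged intubation among the consequences of poorly managed pain. Against this, Section 2 also notes conflicting evidence on respiratory performance. An effect is plausible but not established.

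**4. The plan's own sample size.** For 10 MME, SD 25, two-sided 0.05 and 90% power, the normal approximation is n = 2 × (1.960 + 1.2816)² × 25² / 10² = 131.3, so 132 per group. The t-based figure is 132.3, so 133, as stated. Power at 133 is 0.904. Nothing in this point alters that figure.

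**5. What the synopsis rule could do.** The documents give no exclusion rates and no opioid use for these patients, so every input here is an assumption. Shifts are ropivacaine minus saline. Since benefit means a negative difference, a positive shift shrinks an apparent benefit.

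*Form A.* Let D be the mean MME of excluded minus retained patients, equal in both arms, and p the exclusion rate. Each retained mean falls by pD, so shift = D × (p_saline − p_ropivacaine).
- 10% v 5%: 20 × 0.05 = 1.0 and 60 × 0.05 = 3.0 MME
- 6% v 3%: 20 × 0.03 = 0.6 and 60 × 0.03 = 1.8 MME

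*Form B.* Assume no block effect on MME, and that the block only ever prevents exclusion. Let D be the mean MME of patients excluded only under saline, minus that of patients excluded under neither. Then shift = D × (p_saline − p_ropivacaine) / (1 − p_ropivacaine).
- 10% v 5%, D = 25: 25 × 0.05 / 0.95 = 1.3 MME
- 20% v 10%, D = 50: 50 × 0.10 / 0.90 = 5.6 MME
- 20% v 10%, D = −25: −25 × 0.10 / 0.90 = −2.8 MME

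The sign follows D, and the documents do not say whether these patients use more or fewer opioids.

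**6. Precision.** If 20% of all 340 were excluded and nobody else lost, 272 remain and power is 0.910. If the exclusion fell on top of the full 25% attrition, the base is 340 × 0.75 = 255 (power 0.891), and removing a further 5% to 20% gives power from 0.876 down to 0.815. The documents do not say whether the 25% already covers mITT exclusions.

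**The case against.** The best defence is that the operative plan is already right. Section 7 and the later SAP give the same rule, the estimand includes everyone dosed, and delayed extubation enters only a sensitivity model. On that view the synopsis clause looks like leftover wording and the fault is an inconsistency, not a design decision. This largely stands. It does not make the clause correct, and without a precedence statement a reader of the protocol cannot be sure which population was pre-specified.

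Four stronger readings are tempting but not supported.

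- *The primary comparison will be conditioned on extubation, or two primary results will be reported.* The SAP has one definition and one estimand. Either outcome would require setting them aside for one synopsis clause.
- *The cut-off could be chosen to suit the data.* Protocol 3.7 keeps the clinical team, outcome assessors and data entry staff blinded until lock, and SAP Section 1 has the SAP finalised before lock. The missing cut-off is a gap, but these safeguards limit a data-driven choice.
- *The exclusion would manufacture a benefit.* If more saline patients are removed and they use more opioids, the apparent benefit shrinks. It grows only if they use fewer.
- *Some 11 to 19 patients would be lost from 255.* That takes average exclusion of 4.5% (255 × 0.045 = 11.5) to 7.5% (255 × 0.075 = 19.1) and stacks it on the full 25% attrition. Section 7 ties the 340 to the mITT analysis, so the allowance may already cover such losses.

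The protocol also promises complete intention-to-treat and per-protocol sensitivity analyses. That would be a fair safeguard, but the SAP defines only mITT and safety populations, so it is not carried through.

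**Conclusion.** The contradiction is real and lies in current protocol text. The synopsis applies an undefined exclusion after randomisation and dosing, on an event the block may influence; Section 7, SAP 3.2.1 and the treatment-policy estimand do not. If the synopsis rule were applied, the randomised comparison could be biased.

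Size and direction cannot be computed from the documents. The illustrative shifts, from about −2.8 to +5.6 MME against a design difference of 10 MME, rest entirely on assumed exclusion rates and opioid gaps. They show that the choice of population could matter, not that it will. Because Section 7 and the later SAP agree on the sound definition, this is a consistency error with limited practical risk. It is still worth correcting, because it concerns who counts in the primary result and the correction is cheap.

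**What to change.** - **Synopsis.** Delete the clause excluding patients with prolonged intubation, so that the synopsis matches Section 7 and SAP 3.2.1. The SAP needs no further sentence on this, since 3.2.1 and the estimand already include every randomised and dosed participant.
- **SAP.** Define delayed extubation, as used in SAP 3.1.6 and the 3.4.1 sensitivity analysis, and fix that definition before unblinding.
- **Any analysis without such patients.** Label it supplementary and use the same pre-fixed definition.

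**Cost.** A short protocol correction through the usual ethics-board amendment, and one SAP definition. No new data are needed and the sample size does not change.

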## 2. Introduction and Background

Acute postoperative pain following cardiac surgery remains a prevalent and consequential problem, [1, 2] with the majority of patients experiencing moderate to severe pain during the perioperative period despite treatment with analgesic therapy [3, 4]. Beyond the short-term impact, significant pain in the days following surgery has been demonstrated to be an important predictor of chronic postoperative pain development [5-9], with Fletcher et al. demonstrating that a 30% increase in chronic pain incidence at 12 months occurs with a 10% increase in time spent in severe pain on postoperative day 1 [9]. Indeed, rates of chronic postsurgical pain have been reported as high as 35% at 3 months, 27% at 1 year, and 20% at 3 years postoperatively amongst cardiac surgical patients [10]. Furthermore, insufficiently managed pain has been linked to morbidity and mortality risk, with clinically important sequelae including cardiac, pulmonary, musculoskeletal, and metabolic complications, prolonged intubation and hospital stays, psychological consequences, as well as increased opioid consumption [11-14]. The consequent loss of productivity combined with the health-care costs leads to a significant toll on the healthcare system; in 2008 it was estimated that the annual cost of chronic pain conditions, including postoperative pain, was \$560-635 billion in the U.S. alone [15, 16].

High-dose, short-acting opioid analgesics have been a cornerstone of both intraoperative anesthesia and early postoperative pain management amongst cardiac surgical patients [14, 17, 18]. However, the utilization of short-acting opioids comes at the risk of either inadequate pain control or serious adverse consequences due to the significant fluctuations in blood opioid levels [14, 19]. In particular, potential ramifications of high doses of opioids include respiratory depression, hyperalgesia, dependence/addiction, tolerance, ileus, constipation, and over-sedation [14, 18-20]. Furthermore, previous literature has shown that nearly 10% of post-cardiac surgery patients develop new persistent opioid use [21]. Numerous strategies have been investigated to simultaneously manage postoperative pain management and decrease opioid usage following cardiac surgical procedures; these goals remain important research priorities in this field.

To address the need for additional multimodal analgesic options for post-cardiac surgery patients, there has been growing interest in the role of nerve blocks, and particularly those intervening on the medial aspect of the thorax. Local anesthetic techniques have become a

mainstay of pain control in many surgical specialties [22], but there has been limited evidence definitively confirming their role in cardiac surgery. In one such technique, the superficial parasternal intercostal plane (PIP) block or the pectointercostal fascial plane block (PIFB), local anesthetic is deposited in a plane between the pectoralis major and intercostal muscles under ultrasound guidance to allow for visualization of the anesthetic spread [23, 24]. The anterior branches of the intercostal nerves are the major target for this block [25]. A recent review identified 10 randomized studies investigating the efficacy of parasternal intercostal nerve blocks in cardiac surgery patients, 8 of which specifically studied superficial PIP blocks, and none of which enrolled more than 100 patients [26]. While some centers have implemented these blocks and initial studies are promising for the ability of these interventions to reduce pain or opioid requirements [27-33], this reduction has not reached significance in every trial [29, 31], and there remains some conflict in the literature regarding the ability of these interventions to improve indices of respiratory performance [26, 28, 31, 33, 34].

One of the major limitations of nerve blocks administered via single doses of local anesthetic is their limited duration of action. For example, one prospective study of 113 participants undergoing cardiac surgery receiving ultrasound-guided deep PIP blocks with 40 mL 0.33% ropivacaine demonstrated a mean effective duration of a mere 17 hours [35]. One previous randomized study of 116 patients has investigated the role of continuous superficial PIP blocks in cardiac surgical patients, finding a significant reduction in time to extubation, time to mobilization, length of ICU stay, length of hospitalization, nausea/vomiting, pain scores at rest and with movement, and sufentanil/flurbiprofen consumption [36]. One other study investigated the potential for re-dosing of the superficial PIP block, randomizing 80 patients to ultrasound-guided superficial PIP block versus placebo on postoperative days 0 and 1. The authors demonstrated a reduction in pain scores, but were unable to show a significant reduction in opioid requirements over 48 hours nor incidence of delirium [29].

As such, there is still equipoise on the role of intermittent superficial PIP blocks in the multimodal approach to analgesia following cardiac surgery, and consequently guidelines are limited in the recommendations that can be provided on the use of such interventions [37]. The purpose of the present randomized trial is to definitively establish the clinical efficacy of

intermittent superficial PIP blocks with ropivacaine in optimizing postoperative pain control amongst a large population of patients undergoing cardiac surgery via median sternotomy.

### **3. Study Design**

#### **3.1 Study Overview**

EPOCH CardioLink-10 is a randomized, double-blinded, parallel-group, multicentre study of superficial parasternal intercostal plane blocks with 0.2% ropivacaine versus sham block with 0.9% normal saline administered via catheters placed under ultrasound guidance in patients undergoing cardiac surgery through a median sternotomy. Patients meeting inclusion criteria who provide informed consent will be randomized in a 1:1 fashion into the intervention or control group. Based on the below sample size calculation, approximately 340 patients will need to be randomized to detect important differences. This will be a multicentre trial (up to 4 sites in Canada), with usual institutional anesthetic and postoperative analgesia management being provided to all enrolled patients. Patients will be followed prospectively during the hospitalization with regular assessments of postoperative pain and recovery, as well as during follow-up visits at 6 weeks and 3-6 months following their operation. To reduce lost-to-follow-up, patients will be asked to provide up to two telephone contact numbers.

The four Canadian trial sites are:

- 1) St. Michael's Hospital, Toronto, ON (Recruiting)  
PI: [name]
- 2) QEII Health Sciences Centre, Halifax, NS (Recruiting)  
PIs: [name], [name] [name]
- 3) Foothills Medical Centre, Calgary, AB (Recruiting)  
PI: [name]; Co-I: [name]
- 4) Royal Columbian Hospital, New Westminster, BC (Recruiting)  
PI: [name]; Co-I: [name], MN

